### Economic evaluation

Economic evaluation will be carried out by the trial health economist (SB) and follow the methods developed in the exploratory trial [25]. The evaluation will take a broad perspective, covering use of all hospital, community health and social services, including complementary therapies, plus productivity losses resulting from time off work or reduced productivity at work due to illness. Data on therapist contacts in the MBCT groups will be collected from therapist records to avoid patients revealing their treatment group to the research assessors. Data on indirect time, including preparation and supervision, will be collected directly from the trial therapists. Data on use of other services will be collected using the Adult Service Use Schedule (AD-SUS). The AD-SUS was developed in several mental health trials and was further modified and successfully employed in the exploratory trial. Productivity losses as a result of time off work or reduced productivity at work due to illness will be measured using the absenteeism and presenteeism questions of the World Health Organization's Heath and Work Performance Questionnaire (HPQ) [47].

The cost of the psychosocial treatments will be directly calculated from salaries using the micro-costing approach employed in the exploratory trial. National UK unit costs will be applied to medication, hospital contacts and community health and social services. Productivity losses will be calculated using the human capital approach, which involves multiplying the individual's salary by reported days off work due to illness, but will be explored further in sensitivity analyses to take into consideration concerns that the human capital approach overestimates these costs [48].

A further element to the economic evaluation will be the estimation of the cost of training of therapists. There are few MBCT therapists in the UK and, should the intervention prove cost-effective, policy makers will require evidence of the investment needed to train new therapists. Detailed information will be collected on the resources that currently go into the MBCT postgraduate training programme at the University of Exeter. These costs will be used to model the longer-term and wider cost impact of MBCT on relative cost-effectiveness.

### Statistical analysis plan

Analyses will be conducted by the trial statistician (RT) following CONSORT standards and overseen by the Data Monitoring and Safety Committee. Initial analyses will be conducted on an intention to treat (ITT) basis, with subsequent analyses being per protocol. All statistical models will be run with and without adjustment for baseline characteristics where the covariate selection is derived from comparison of the treatment groups at baseline.

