***Randomisation ***will use permuted block randomisation using computer generated quasi-random numbers. Randomisation will be stratified according to recruitment locality (4 sites, enabling a steady flow to treatment groups) and participants' symptomatic status at intake assessment (asymptomatic *vs*. partially symptomatic), using the GRID-Hamilton Rating Scale for Depression GRID-HAMD [31] cut-off of less than eight being asymptomatic and greater than or equal to 8 being partially symptomatic.

Figure 1 summarises the trial Consort diagram.

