### Sample size

Different relapse prevention interventions with different populations produce different absolute rates of depressive relapse/recurrence. Therefore, we have based our sample size on estimated hazard ratios for MBCT *vs*. m-ADM rather than estimated absolute relapse/recurrence rates. We canvassed service users and clinicians who concurred that a relative reduction in relapse/recurrence of 10% would be clinically important. ***(i) The policy question: ***The systematic review of MBCT *vs*. usual care for patients with recurrent depression reports hazard ratios of .47 and .28 for the key trials [24]. We applied several conservative assumptions (first row of Table 1). First, even though the exploratory trial data suggest that the hazard ratio was improving in favour of MBCT as the length of follow-up increased [25], we assumed the hazard ratio of .63 at 15 months to power the proposed trial at 24-months follow up. Second even though attrition from MBCT trials to date is consistently <15%, we have assumed an attrition rate of 20% over the 24-months of follow-up. Finally, we assumed there may be a small clustering effect (ICC = 0.01). The resultant sample size calculation assumptions and output are shown in Table 1 based on 80% power and significance set at .05. This leads to a total sample size of 420 across the two groups.

**Table 1 T1:** Sample size calculation

Author	Comparison	Mean hazard ratio	ICC	Design factor**	Attrition rate	**Sample size per group**^**a**^
Conservative scenario	MBCT *vs*. m-ADM	0.63	.01	1.11	20%	210

Kuyken et al., 2008 [25]	MBCT *vs*. m-ADM	0.63	-0.02	1.0	7%^a^	160

Ma & Teasdale, 2004 [22]	MBCT *vs*. usual care	0.28	-0.008	1.0	3%^b^	14^c^

Teasdale et al., 2000 [23]	MBCT *vs*. usual care	0.47	-0.04	1.0	5%^b^	41^c^

Sample size necessary for 90% power at 5% significance at 24 months;

^a ^at 15 months; ^b ^at 60 weeks, ^c^assuming exponential survival function.

Note group size of 12

***For the secondary outcomes***, meta-analyses of generic mindfulness approaches suggest medium effect sizes in changes in depressive symptoms [19,40] and our exploratory trial suggests medium effect sizes for the secondary outcomes of residual depressive symptoms, psychiatric co-morbidity and quality of life [25]. The sample size estimate for our policy question will enable us to detect a medium between-groups effect size (standardised mean difference or Cohen's d = 0.40) on the main secondary outcomes.

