#### (i) The policy question

For the primary outcome variable, time to relapse/recurrence will be compared using Cox regression proportional hazard survival analysis with treatment condition (MBCT/m-ADM) as the independent variable and allowing for the stratification variables. In a secondary analysis ADM use will be added as an independent variable in the Cox regression model. A per protocol analysis will also be undertaken for the secondary outcomes.

Secondary outcomes will be examined using mixed models Analysis of Variance (ANOVA): between group (ITT/per protocol) and repeated measures (3-24 month follow-ups). Sensitivity analyses will explore the impact of imputation of data losses including loss to follow up and drop out.

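### Covariates beyond the stratification factors are to be chosen by comparing the arms at baseline, which picks up chance imbalance; the plan should name them in advance and say which model is primary.

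*Protocol article*

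**What the plan says.** The opening paragraph of the Statistical analysis plan section states: "All statistical models will be run with and without adjustment for baseline characteristics". The same sentence adds that "the covariate selection is derived from comparison of the treatment groups at baseline". It gives no list of covariates, no cut-off for the comparison and no prognostic criterion. On analysis sets it says: "Initial analyses will be conducted on an intention to treat (ITT) basis, with subsequent analyses being per protocol".

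Under (i) The policy question, time to relapse/recurrence is analysed by Cox regression with treatment "as the independent variable and allowing for the stratification variables". The section on setting and randomisation identifies those variables: "Randomisation will be stratified according to recruitment locality" (four sites) and by "symptomatic status at intake assessment" (GRID-HAMD below 8 against 8 or more). A further Cox model with antidepressant use added is called secondary.

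The secondary outcomes go to mixed-model ANOVA over the 3 to 24 month follow-ups. Neither a baseline term nor the stratification variables are named for those models.

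**The concern.** Treatment is allocated by permuted-block randomisation, so a baseline difference between the arms is a chance event. A covariate improves the treatment comparison because it predicts the outcome, not because it differs between arms. A rule based on imbalance can therefore bring in irrelevant variables and leave out strong predictors that happen to be balanced. The list also cannot be written down until the baseline data have been divided by arm, even if arm labels are masked, so the model cannot be fixed in advance.

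The consequence is clearest for the secondary outcomes. The baseline value of a symptom or quality-of-life score is normally a natural predictor of its later values. Under this rule it would enter only if the arms happened to differ on it.

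Each model also yields two results and the opening paragraph ranks neither. In a Cox model the two hazard ratios are different quantities (non-collapsibility) and can diverge without any imbalance, so the plan needs to say which one is the result.

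This is a stated rule, not a detail left to a fuller document. A separate SAP would either inherit it or contradict the published text.

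**Working it through.** No figure printed in the article is in dispute here, so there is none to reproduce. The checks ask how the rule behaves and what pre-specification would gain.

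**Inputs from the article.** N = 420; attrition 20%, so 420 × 0.80 = 336 followed; planning hazard ratio 0.63 ("we assumed the hazard ratio of .63 at 15 months"); exploratory-trial relapse at 15 months of 60% (m-ADM) and 47% (MBCT). Those proportions imply, under proportional hazards, ln(0.53)/ln(0.40) = 0.69, used as a second value. 

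**Assumptions.** The 5% selection cut-off, number of candidates, covariate strengths and exponential relapse times are not in the article.

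**1. How often the rule selects something.** With k independent candidates, the chance of at least one selection is 1 − 0.95^k: 23% for k = 5, 40% for 10, 54% for 15 and 64% for 20. If three candidates are truly prognostic, the chance that any of them is selected is 1 − 0.95³ = 14%. A single named baseline score would enter 5% of the time.

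**2. Relapse: a finer version of the stratifying variable.** 336 patients, 60% control relapse at 15 months, censoring at 24 months, stratum formed by a median split, 1,200 runs per cell. Power in %:

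| HR | Covariate log-HR per SD | No covariate | Stratum in model | Continuous covariate | Gain over stratum |
|---|---|---|---|---|---|
| 0.63 | 0.3 | 91 | 93 | 94 | 1 |
| 0.63 | 0.5 | 87 | 91 | 92 | 1 |
| 0.63 | 0.7 | 84 | 90 | 94 | 4 |
| 0.69 | 0.3 | 79 | 80 | 82 | 2 |
| 0.69 | 0.5 | 70 | 76 | 78 | 2 |
| 0.69 | 0.7 | 66 | 75 | 79 | 4 |

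A separate simulation gave gains of about 0 to 3 points at HR 0.63 and 2 to 7 at HR 0.69. Monte Carlo error is about 1 point per cell: √(0.9 × 0.1/1,200) = 0.009.

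**3. Relapse: a predictor beyond the stratum.** Stratum term in every model, 15 further candidates of which one is prognostic, 1,500 runs per setting. Power in %:

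| HR | Covariate log-HR per SD | Stratum only | Imbalance-selected | Pre-specified |
|---|---|---|---|---|
| 0.63 | 0.3 | 91 | 91 | 93 |
| 0.63 | 0.5 | 88 | 89 | 93 |
| 0.63 | 0.7 | 82 | 82 | 92 |
| 0.69 | 0.3 | 77 | 76 | 81 |
| 0.69 | 0.5 | 69 | 70 | 79 |
| 0.69 | 0.7 | 65 | 65 | 80 |

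The rule moves power by at most 1 point. Pre-specification adds 2 to 10 points at HR 0.63 and 4 to 15 at HR 0.69. The separate simulation put the largest gain at about 14 to 16.

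**4. Continuous outcomes.** Linear model, N = 420, standardised effect 0.25, three prognostic covariates among 10 or 20 candidates explaining R² of 0.1 to 0.3, 8,000 runs per scenario. Simulated power was 72 to 73% unadjusted, 73 to 74% with imbalance selection, and 77% (R² 0.1) to 86% (R² 0.3) with pre-specification. A formula check agrees. SE = 2/√420 = 0.0976, so z = 0.25/0.0976 = 2.56 and power is Φ(2.56 − 1.96) = 73%. Dividing z by √0.9 and √0.7 gives 77% and 86%.

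At the article's own effect size of 0.40 with 336 followed, ignoring clustering, z = 0.40/(2/√336) = 3.67 and power is already Φ(1.71) = 96%. There the gain is mainly precision: intervals narrower by 1 − √0.9 = 5% to 1 − √0.7 = 16%.

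**5. Type I error (same linear simulation).** Imbalance-selected model 4.0 to 4.5%; better of the adjusted and unadjusted versions 5.2 to 5.4%.

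**The case against.** The strongest reply is that the primary analysis is largely protected. The Cox model is specified "allowing for the stratification variables", so locality and baseline symptom status are in it whatever the baseline tables show. A reader might infer from the opening paragraph that chance imbalances replace prognostic factors altogether; the text does not support that. This part of the reply stands, and the point is limited to additional covariates.

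It can also be said that the primary model is identifiable. The policy-question section gives one Cox model, calls the model with antidepressant use secondary, and ITT comes first. That is a natural reading, and it narrows the ambiguity. It does not remove it, because the with-and-without instruction covers all models and nothing labels either version.

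A third reply is that the harm is small. A reader might infer a routine loss of 4 to 15 points of power. The upper end needs a strong predictor unrelated to the stratum and an HR of 0.69, which is not the planning value; comparing with a model that has no covariates also overstates the loss, because the stratum is already in. Nor is the 54% for 15 candidates a false-positive rate for treatment: it is the chance that some variable is picked, under an assumed 5% test. This reply stands on magnitude. It does not defend the rule, which still gains nothing.

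**Conclusion.** The point holds in limited form. For covariates beyond the stratification factors, and for the baseline scores in the secondary models, the selection rule rests on the wrong criterion, cannot be fixed in advance and brings essentially no precision. The primary model is implied but not labelled.

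The size is modest. With the stratum already in the Cox model and HR 0.63, continuous GRID-HAMD would add about 0 to 3 points of power (up to 4 in one simulation). More is available only from a strong predictor unrelated to the stratum, and the article gives no evidence of how strong any covariate is. A reader might infer serious alpha inflation from having two versions; the simulated 5.2 to 5.4% does not support that, with the caveat that it comes from a linear-model analogue and not from the Cox model. All power figures rest on assumed covariate strengths, an assumed 5% cut-off and exponential relapse times. The plan should be corrected, but the validity of the primary comparison is not threatened.

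**What to change.** Delete the rule that derives covariates from the baseline comparison. State that the Cox model with treatment and the stratification variables gives the primary result. Before unblinding, name any further covariates on prognostic grounds, for example baseline GRID-HAMD as a continuous score and, for each continuous secondary outcome measured at baseline, its baseline value. State for every outcome which version is the main one and label the other supportive; for the continuous secondary outcomes the baseline-adjusted model is the natural main version.

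The cost is one or two sentences in the plan. No new data are needed and N stays at 420. Baseline tables by arm can still be reported descriptively.

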#### (i) The policy question

For the primary outcome variable, time to relapse/recurrence will be compared using Cox regression proportional hazard survival analysis with treatment condition (MBCT/m-ADM) as the independent variable and allowing for the stratification variables. In a secondary analysis ADM use will be added as an independent variable in the Cox regression model. A per protocol analysis will also be undertaken for the secondary outcomes.

Secondary outcomes will be examined using mixed models Analysis of Variance (ANOVA): between group (ITT/per protocol) and repeated measures (3-24 month follow-ups). Sensitivity analyses will explore the impact of imputation of data losses including loss to follow up and drop out.

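### Free improvement: prespecify the continuous intake GRID-HAMD score in the primary Cox model, beside the two-level stratum (below 8 versus 8 or more)

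*Protocol article*

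**What the plan says.** Three statements in the protocol article bear on this.

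- **Randomisation** (Setting, participants, recruitment and randomization). Allocation is stratified by four localities and by "participants' symptomatic status at intake assessment (asymptomatic" versus partially symptomatic), with a GRID-HAMD "cut-off of less than eight being asymptomatic and greater than or equal to 8 being partially symptomatic".
- **Primary model** (Statistical analysis plan, (i) The policy question). Time to relapse/recurrence is analysed by Cox regression "with treatment condition (MBCT/m-ADM) as the independent variable and allowing for the stratification variables". Whether those variables enter as covariates or as strata of the baseline hazard, symptom status has two levels.
- **Further adjustment** (opening of the Statistical analysis plan). The rule, which refers to how the arms compare on entry, is: "All statistical models will be run with and without adjustment for baseline characteristics where the covariate selection is derived from comparison of the treatment groups".

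The continuous intake score is therefore neither prespecified for the primary model nor excluded from the adjusted runs. The Sample size section claims no gain from covariate adjustment.

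**The concern.** A cut at 8 is needed to stratify randomisation, but not in a regression. In the named model, scores of 0 and 7 carry the same symptom-related risk, as do 8 and any higher eligible score, while 7 and 8 are separated by a step. If relapse risk rises with the score inside either category, the model leaves that information unused.

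The general adjustment rule does not reliably recover it. That rule responds to an observed difference between arms, and stratifying on the cut score makes such a difference less likely. A score that predicts relapse well but is balanced would stay out.

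At stake is a little power for the primary comparison, recoverable without an extra patient or measurement.

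**Working it through.** **1. Inputs from the article.** Hazard ratio: "we assumed the hazard ratio of .63 at 15 months to power the proposed trial at 24-months follow up". Attrition: "we have assumed an attrition rate of 20% over the 24-months of follow-up". Design factor 1.11; 210 per group, 420 in total. Significance level 0.05, taken as two-sided because the article does not say. Power is given as "based on 80% power and significance set at .05" in the text and as "Sample size necessary for 90% power at 5% significance at 24 months" under Table 1; that conflict is a separate matter. Control relapse is taken as 60%, the 15-month m-ADM figure from the exploratory trial.

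**2. Reproducing the plan's own figure.**
- Freedman events at 80% power: (1.960 + 0.842)² × (1 + 0.63)² / (1 − 0.63)² = 7.849 × 2.6569 / 0.1369 = 152.3, so 153.
- MBCT relapse under proportional hazards: 1 − 0.40^0.63 = 43.9%. Mean over arms: (0.600 + 0.439)/2 = 0.519.
- Per arm: 153 / 0.519 / 2 = 147.3. Inflated: 147.3 × 1.11 / 0.80 = 204.4, so 205.
- Comparing the two proportions (60% versus 43.9%) needs 150 per arm: 150 × 1.11 / 0.80 = 208.1, so 209.

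Both are within 3% of 210. The figure is not unique to 80% power: Freedman at 90%, with 60% extended exponentially from 15 to 24 months (76.9% versus 60.3%), gives 206.3, so 207. None of these routes uses covariate adjustment, so the sample size does not depend on this point.

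**3. Information available.** Effective patients: 420 × 0.80 / 1.11 = 303. Events: 303 × 0.519 = about 157. Closed-form check: √(157.2/4) × |ln 0.63| = 6.269 × 0.462 = 2.896; 2.896 − 1.960 = 0.936; power 82.5%. The simulated baseline below (82.9%) agrees.

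**4. Simulation of the change.** 5,000 trials per row, 303 patients, hazard ratio 0.63, randomisation stratified on the binary score. Assumed, because the article gives neither: the prognostic strength, and a right-skewed score with about 28% of patients in the upper stratum. Locality was not modelled.

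| Assumed effect of the score on relapse | Power, stratum only | Power, stratum + score | Gain in points (simulation SE) |
|---|---|---|---|
| None (HR 1.0 per SD) | 82.9% | 82.8% | −0.04 (0.16) |
| HR 1.2 per SD | 82.0% | 82.3% | 0.32 (0.22) |
| HR 1.4 per SD | 81.4% | 82.8% | 1.42 (0.29) |
| HR 1.6 per SD | 79.5% | 82.1% | 2.60 (0.36) |
| HR 2.0 per SD (outer end) | 77.4% | 82.5% | 5.06 (0.43) |
| Step at the cut-off only, HR 2 | 81.8% | 82.0% | 0.20 (0.15) |

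The stratum itself earns power: at HR 1.4 per SD, no adjustment gives 79.9% and the stratum alone 81.4%.

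**5. Second set of assumptions.** Another simulation (2,500 trials per slope) used all 420 patients, 20% dropout, no design factor, four localities, about 200 events, and an assumed score mean of 6 and SD of 4.5.

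| Log-hazard slope per SD (HR) | Power, stratum only → with score | Gain, points | Estimated HR, stratum only → with score |
|---|---|---|---|
| 0.20 (1.22) | 90.0% → 90.2% | 0.2 | 0.626 → 0.624 |
| 0.35 (1.42) | 88.8% → 89.4% | 0.6 | 0.634 → 0.630 |
| 0.50 (1.65) | 88.5% → 89.9% | 1.4 | 0.633 → 0.624 |

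Direction and order of size agree. The gains are smaller here, where power starts near 90%.

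**The case against.** The strongest reply is that nothing here is wrong. Analysing by the factors used to stratify randomisation is standard and matches the design, and a condensed article may leave the functional form of a covariate to the full analysis plan. The benefit also rests on assumed inputs. A log-linear effect favours the continuous form from the start, and excluding currently depressed patients limits high scores, so the spread within strata is unknown. All of this stands, and it is why the point is an optional improvement. What remains is that the article does name the covariates of the primary model, and symptoms are among them only at two levels.

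A reader might infer more than the article supports:

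- **That the plan gives up power for nothing.** It does not: the stratum belongs in the model and gains power itself. Only the unused remainder of the score is at issue, and that may be worth nothing.
- **That chance differences in symptoms within strata can never be corrected.** The general adjustment rule can bring the score in if the arms differ at baseline. Its limit is that it responds to imbalance, not to prognosis.
- **That the trial stratified on symptoms because it expected them to predict relapse.** The article gives a reason for stratifying by locality but none for symptoms.
- **That the hazard ratio is materially pulled towards 1.** With a true value of 0.63, the stratum-only model gave 0.626 to 0.634, all within 0.004 of it. Adding the score moved the estimate by at most 0.009 (0.633 to 0.624), and in two of three scenarios further from 0.63.

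**Conclusion.** The point holds as a low-priority, nearly costless improvement. The named primary model uses baseline GRID-HAMD only at two levels, and nothing in the article brings the continuous score in on prognostic grounds.

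With about 157 events and power near 80%, adding it is worth about 0 points if the score adds nothing within strata, roughly 0.3 to 1.5 points at a hazard ratio of 1.2 to 1.4 per SD, and about 2.6 points at 1.6. There is no material loss if the score is not prognostic or if the true effect is a step at 8. These sizes depend on an assumed prognostic strength, score distribution and 60% control relapse, so the article cannot show that any gain will occur. No figure in the protocol is wrong because of this.

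**What to change.** Keep the cut at 8 for randomisation, and keep locality and the stratum in the primary Cox model. Add the continuous intake GRID-HAMD score to that model as a prespecified covariate, either linear or as a simple spline whose form is fixed in advance, and state that this is the main analysis whatever the baseline comparison shows. Fix it before unblinding. In practice that means before relapse is first compared by arm, and the plan schedules a primary outcome analysis at 12 months.

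The cost is one line in the analysis plan and one extra model term (a few for a spline), with no new data. The reported hazard ratio would then also be conditional on the score; the simulated shift was at most 0.009. If the full analysis plan already specifies this, the sponsor need only confirm it.

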## Methods/Design

### Design

The design is a single blind, parallel RCT examining MBCT vs. m-ADM with an embedded process study. To answer the main policy research question: "Is MBCT superior to maintenance antidepressant medication (m-ADM) in preventing depression over 24 months?" the proposed trial compares MBCT plus ADM-tapering with m-ADM for patients with recurrent depression. Depressive relapse/recurrence over two years is the primary outcome variable.

The trial will answer the explanatory question "Is an increase in mindfulness skills the key mechanism of change?" in two mutually informative ways: quantitative measurement of potential mediating variables pre/post-treatment [28] and an embedded qualitative study to elicit service users' experiences of treatment.

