##### ADM tapering in the MBCT arm: Rationale and protocol

The rationale for this trial is the development of a psychosocial intervention for the prevention of depressive relapse/recurrence that provides an *alternative *to the current treatment of choice, m-ADM. Consequently, once patients in the MBCT arm of the trial have learned skills for preventing relapse/recurrence, they will be invited to taper ADM with GP support. A protocol for ADM tapering was developed in the exploratory trial in accordance with NICE guidance regarding information provided to the patient, time course, monitoring of discontinuation/withdrawal symptoms, and consideration of the drugs half-life. In the exploratory trial over the follow-up period (*circa *450 days), the mean number of days on ADM was significantly different across the two groups: m-ADM, M = 411.4 > MBCT, M = 266.46; t = 5.40, *p *< 0.0001. Six months after the end of MBCT 75% of the patients in the MBCT arm of the trial had successfully discontinued their medication. These data testify to the relative success of the tapering/discontinuation regime established in the exploratory trial. However, they also highlight the pragmatic reality that some GPs and/or patients will choose not to taper and we have therefore introduced ADM use as a secondary outcome and the analysis plan will examine this variable in the primary and secondary analyses. We will encourage patients to discontinue their medication within 6 months of the end of their MBCT group.

The MBCT manual has been adapted to include more work on developing a relapse signature and response plan that explicitly includes discontinuation/resumption of ADM. If patients in the MBCT arm experience a significant deterioration following tapering, they will be encouraged to use the skills they learned in MBCT.

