#### (ii) The explanatory questions

These will be examined using a mix of three mutually informative methods:

(a) For the MBCT arm time to relapse/recurrence of depression will be compared using Cox regression proportional hazard survival analysis, allowing for the stratification variables and any group differences in ADM tapering/usage (if rates of tapering/usage are different across the two arms).

(b) Mediational analyses will investigate hypothesised mechanisms of change pre-/post-treatment across the trial arms using approaches to testing mediation that allow multiple mediators in one model using the approach set out by Kraemer et al. (2002) and as used in our exploratory trial [49].

(c) Qualitative data will be analysed using thematic analysis (with NVivo software). This will combine inductive and deductive approaches and will be conducted collaboratively by a small sub-group of the research team in order to enhance validity.

The Data Monitoring and Safety Committee will oversee analysis at 3 and 12 months for patient safety and at 12 and 24 months for the primary outcome analyses. Given the public health importance of the findings we anticipate disseminating the findings at 12 and 24 month follow-ups as soon as they are available.

(d) Differences in mean costs will be analysed using standard parametric t-tests with the validity of results confirmed using bias-corrected, nonparametric bootstrapping (repeat re-sampling) [50]. Despite the skewed nature of cost data, this approach is recommended to enable inferences to be made about the arithmetic mean [51]. The primary economic analysis will focus on the policy question: MBCT vs. mADM. Cost-effectiveness will be assessed through the calculation of incremental cost-effectiveness ratios (ICER) and will be explored in terms of relapse/recurrence and quality adjusted life years using the EQ-5D measure of health-related quality of life. Uncertainty around the cost and effectiveness estimates will be represented by cost-effectiveness acceptability curves [52].

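### The secondary Cox model that adds ADM use does not give a valid effect of MBCT independent of medication: its bias can go either way, and explanatory analysis (a) contradicts itself

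*Protocol article*

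**What the plan says.** The Design section defines the contrast as a strategy: "the proposed trial compares MBCT plus ADM-tapering with m-ADM for patients with recurrent depression". Under ADM tapering in the MBCT arm, patients who have completed the skills training are told that "they will be invited to taper ADM with GP support", and the target is: "We will encourage patients to discontinue their medication within 6 months of the end of their MBCT group". The same section accepts that "some GPs and/or patients will choose not to taper and we have therefore introduced ADM use as a secondary outcome". It also says that the relapse response plan covers both stopping and restarting ADM.

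Under (i) The policy question, the primary Cox model is specified "with treatment condition (MBCT/m-ADM) as the independent variable and allowing for the stratification variables". The next sentence reads: "In a secondary analysis ADM use will be added as an independent variable in the Cox regression model". The article does not say how ADM use is coded, at what time it is measured, or what the adjusted arm coefficient is meant to estimate.

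Under (ii) The explanatory questions, item (a) reads: "For the MBCT arm time to relapse/recurrence of depression will be compared using Cox regression". It allows for the stratification variables and for "any group differences in ADM tapering/usage (if rates of tapering/usage are different across the two arms").

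**The concern.** ADM use differs from a baseline covariate in three ways.

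- It is part of what is being tested. Holding it fixed removes part of the MBCT-plus-tapering strategy from the comparison.
- It is chosen. If patients who stay on ADM differ in prognosis from those who stop, conditioning on ADM use breaks the balance that randomisation gave.
- It can respond to the outcome. Tapering takes months, so a patient may relapse before stopping and be recorded as a continuing user. A patient who stopped may restart after relapse.

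ADM use is also strongly tied to arm, so error in its coefficient passes into the arm coefficient. At stake is an adjusted hazard ratio, reported beside the policy result, that a reader could take as the effect of MBCT with medication held constant.

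Item (a) has a separate problem: what it compares and what it adjusts for do not fit together.

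**Working it through.** The article gives no figure for this model, so there is none to reproduce. The check asks what the arm hazard ratio (HR) becomes when the truth is known.

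**Inputs from the article**
- 210 per group; 20% attrition, so 210 × 0.80 = 168 per group (Sample size).
- Relapse 60% on m-ADM at 15 months (Our exploratory trial). With a constant hazard this is −ln(0.40)/15 = 0.061 per month.
- 75% of MBCT patients off ADM six months after MBCT, so about 25% still on (ADM tapering section).
- Mean days on ADM out of about 450: 411.4/450 = 91% on m-ADM and 266.46/450 = 59% on MBCT.
- Tapering window: up to about 1 month to the start of the group, about 2 months of group, then up to 6 months, so roughly months 3 to 9.

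**Assumptions not in the article:** exponential survival; 10% of m-ADM patients stop; relapse before the planned taper means no taper; the confounder strengths and restart rates below. Using 91% as the share of m-ADM patients on ADM is a crude conversion from mean days.

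**Why coding matters.** At that hazard, 1 − 0.40^(3/15) = 17% of patients relapse before month 3 and 1 − 0.40^(9/15) = 42% before month 9. Under *ever stopped*, early relapsers count as never having stopped, and every stopper was relapse-free until stopping. That is immortal time.

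**Set 1: neither MBCT nor ADM affects relapse; 210 per arm; tapering in months 3 to 9**

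| ADM use in the model | Arm HR |
|---|---|
| Not included | 0.99–1.01 |
| Ever stopped, 85% taper | about 2.2 |
| Ever stopped, 75% taper | about 1.7 |
| Time-updated, no confounding | 1.00–1.01 (4–5% rejection) |
| 9-month landmark, no confounding | 0.99–1.00 (4–6% rejection) |
| Time-updated, sicker patients less likely to taper (log-odds 1.0 per SD; relapse HR 1.5–2.0 per SD) | 1.07–1.12 |

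With *ever stopped*, the true null was rejected in more than nine of ten simulated trials at either tapering rate.

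**Set 2: same null; ADM use as one fixed value per patient, 25% on MBCT and 91% on m-ADM; 60% relapse; 168 per arm**

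| Mechanism | Arm HR | False conclusion |
|---|---|---|
| No common cause, no restart | 1.00 | 1.8% harmful |
| Sicker patients stay on (log-odds 0.5–1.5 per SD; relapse HR 1.5–2.0 per SD) | 1.13–1.56 | 9–71% harmful |
| 30%, 50% or 70% of relapsers off ADM restart and count as users | 1.33, 1.49, 1.61 | 41%, 73%, 91% harmful |
| Sicker patients stop (log-odds 1.0 per SD; relapse HR 1.5 per SD) | 0.80 | 20% beneficial |
| Days on ADM up to relapse or censoring as the covariate | 0.28 | strongly favours MBCT |

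**Set 3: ADM protective (HR 0.70).** If MBCT skills have HR 0.79 and the strategy is null overall (HR 1.00), the adjusted HR is 0.79 without confounding and 0.99 to 1.15 with it. If the skills do nothing, the strategy HR is 1.26 and the adjusted HR is 0.99. So even an unconfounded adjusted model answers a different question from the policy one, and a confounded one answers neither.

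**Item (a).** The opening restricts the analysis to the MBCT arm and names no comparator. The adjustment is for a difference between the arms, which is constant within one arm and cannot be adjusted for there. If a two-arm model was meant, it is the policy-question model with ADM use again. Item (a) names no mindfulness variable, although it is listed as a method for the mindfulness question.

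**The case against.** The best defence is that the article says only that ADM use is added. A condensed article may leave coding to the analysis plan, and a time-updated or landmark version removes the immortal-time bias. That stands: without confounding those versions return about 1.0. It does not settle the matter. They leave confounding by symptoms untouched, and the coefficient still conditions on part of the strategy.

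Four stronger readings are tempting, and the article does not support them.

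- A reader might infer that the model will make MBCT look harmful, with an HR of 2.2 or more. That needs 85% tapering and a whole-follow-up coding. The article's 85% is attendance at four or more sessions; its discontinuation figure is 75%. Share of time on ADM with restart at relapse gives roughly 2.0 to 3.2, again under a coding the article does not state. Other mechanisms push the HR below 1.
- A reader might infer that the primary result is compromised. The tapering section says ADM use will be examined in both the primary and the secondary analyses, but the stated primary model contains only arm and stratification variables.
- A reader might infer that the mindfulness question goes unanswered. Item (b) and Process data already plan mediation analysis of change scores measured before the outcome.
- A reader might infer that better modelling needs no new data. Adherence comes from self-report and GP database checks at 12 and 24 months, and the article does not say that stop and restart dates are captured.

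**Conclusion.** The point holds for the secondary model. ADM use is a chosen, post-randomisation component of the MBCT strategy that can respond to relapse, so the ADM-adjusted arm coefficient cannot be read as the effect of MBCT independent of medication. This follows from the article's own description and does not depend on any simulation.

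The size does depend on assumptions. Under a complete null, the arm HR is about 1.7 to 2.2 for *ever stopped* with 75% to 85% tapering. For time-updated use it is about 1.0 without confounding and about 1.1 with the confounding assumed above. It falls below 1 if sicker patients stop, or if raw days on ADM up to relapse are used. Tapering timing, confounder strength and restart rates are assumed throughout.

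The consequence is limited: the model is labelled secondary and the intention-to-treat primary analysis stands. Item (a) is a genuine internal contradiction, but one of wording and specification rather than a gap in the mindfulness analysis.

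**What to change.** 1. State that the Cox model without ADM use is the only answer to the policy question, and report ADM use by arm as the secondary outcome it already is.
2. Either drop the ADM-adjusted model or keep it labelled exploratory. If kept, use only ADM exposure before relapse, time-updated or at a landmark; account for earlier symptoms, for example with a marginal structural Cox model; and state what the coefficient estimates. A landmark or time-updated coding alone removes immortal time but not confounding.
3. Before committing to that, confirm that the AD-SUS and GP records give usable stop and restart dates. If they do not, drop the model.
4. Delete item (a), since item (b) covers mediation, or restate it as a within-MBCT-arm model of relapse after the post-treatment assessment on change in mindfulness.

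Cost: items 1 and 4 are wording. Item 2 adds analysis only if the model is kept. The primary analysis and sample size do not change. Whether the planned data suffice for item 2 depends on item 3.
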